### Population

We aim to include a total of 96 patients (n = 48 per group) undergoing elective cardiac surgery for ischaemic and/or valvular heart disease and receiving the allocated study investigational medicinal product (IMP).

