#### Exclusion criteria

The exclusion criteria are as follows:Inability to provide informed consentPregnancy or breastfeedingPreoperative left ventricular ejection fraction (LVEF) < 30%Pre-existing renal insufficiency with an estimated glomerular filtration rate (eGFR) < 30 ml/min/1.73 m^2^Postoperative mechanical circulatory support devices such as left ventricular assist device (LVAD), intra-aortic balloon pump (IABP), Impella, or extracorporeal membrane oxygenation (ECMO) devicePre-existing serum sodium level of > 145 mmol/L or < 135 mmol/LPre-existing serum chloraemia > 111 mmol/L or < 96 mmol/LSystemic steroid therapy (at any dose at time of inclusion)Chronic liver disease (bilirubin > 3 mg/dl)Any signs of infection or sepsis defined as clear clinical evidence for active infection or current antibiotic therapy

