#### Exploratory outcomes

Exploratory outcomes are to assess whether the use of HS results in:A change in acid-base parameters and electrolyte levels as well as inflammatory/immune function indicesDifferences in clinical outcome comparators, including body composition analysis (water balance) using bioimpedance, need for renal replacement therapy, time on the ventilator, length of ICU and hospital stays, as well as ICU mortality and in-hospital mortality. We will also analyse 30-day and 90-day mortality.

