#### Statistical methods

This is a classic two-group study with parallel groups. Whether HS results in less total fluid volume will be assessed by the Mann-Whitney *U* test. Interval variables between groups will be compared using Student’s *t* test or the Mann-Whitney *U* test as appropriate. Fisher’s test for exact probability will be used for the nominal scale data. In the event of an uneven baseline situation, multivariable regression (linear regression for interval outcomes and logistic regression for dichotomous outcomes) will be used for adjustment of baseline differences.

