### Strengths and limitations

To our knowledge, this is the first randomised controlled trial comparing two different saline solutions (7.3% versus 0.9%) in cardiac surgical patients in the ICU. The preliminary character of the study will allow further hypothesis generation in other areas, such as emergency cardiac surgery or sepsis.

Because this study will be performed at a single tertiary care centre, the external validity is limited. In addition, note that this is a preliminary study, so the number of patients included is limited. A further limitation of our study arises from the exclusion of sick patients.

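### If baseline is uneven, ordinary multivariable logistic regression is prescribed for exploratory outcomes (renal replacement, deaths) that may be too rare in 48 patients per arm to give a usable treatment odds ratio

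*Protocol article*

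**What the plan says.** The Statistical methods section of the protocol article sets out two layers of analysis for categorical data. The main one is Fisher's: its "test for exact probability will be used for the nominal scale data". The second is conditional and applies only "In the event of an uneven baseline situation". Once that condition is met, the article states that "multivariable regression (linear regression for interval outcomes and logistic regression for dichotomous outcomes) will be used for adjustment of baseline differences". The section gives no criterion for unevenness. It also names no minimum number of events and no penalised or exact alternative for the logistic model.

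The dichotomous outcomes are found under Exploratory outcomes. That list includes "need for renal replacement therapy, time on the ventilator, length of ICU and hospital stays, as well as ICU mortality and in-hospital mortality", of which renal replacement and the two mortality items are binary. It then adds: "We will also analyse 30-day and 90-day mortality".

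On numbers and risk, the Population section states: "We aim to include a total of 96 patients (n = 48 per group) undergoing elective cardiac surgery". The Exclusion criteria remove, among others, patients with an ejection fraction below 30%, an eGFR below 30, signs of infection or postoperative mechanical circulatory support. Under Strengths and limitations the authors write: "A further limitation of our study arises from the exclusion of sick patients". No expected rate is given for any binary outcome.

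**The concern.** Maximum-likelihood logistic regression needs events in both arms to yield a finite treatment odds ratio, and several events per parameter to yield a stable one. The binary outcomes here are death and dialysis in 96 elective patients, from whom the highest-risk groups have been removed. Few events are a fair expectation, though the documents do not quantify it.

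If an arm has no event, the estimated odds ratio is zero or infinite. If neither arm has one, it is undefined. With a handful of events it may be finite but far from 1 by chance. The article says the model will be used once baseline is judged uneven, so following it could add an unusable or misleading adjusted figure for death or dialysis beside a valid Fisher test. It could also prompt a change of method after the data are seen. Readers will look at these outcomes for reassurance about safety, even though they are labelled exploratory.

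**Working it through.** **The plan's own figure.** The only sample size calculation concerns the primary endpoint: a difference of 1000 ml, SD 1734 ml, alpha 0.05 (sidedness not stated, two-sided assumed) and power 80%. With n = 2(1.960 + 0.842)² × 1734²/1000² = 47.2, rounded up, this gives 48 per group, as stated. It does not bear on the binary outcomes, for which the plan gives no figure to reproduce.

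**Inputs.** There are 48 patients per arm (Population). The event rate p is an assumption, because the documents give none. It is varied from 1% to 10% and taken as equal in both arms.

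**When the treatment estimate does not exist.** An arm without events is enough to make the treatment coefficient non-finite or undefined, whatever covariates are in the model. With q = (1 − p)^48 as the chance of no event in one arm, the chance that at least one arm has none is 1 − (1 − q)². For example, at p = 2%, q = 0.98^48 = 0.379 and 1 − (1 − 0.379)² = 0.61.

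| Assumed rate | Expected events in 96 | q | At least one arm without events |
|---|---|---|---|
| 1% | 1.0 | 0.617 | 85% |
| 2% | 1.9 | 0.379 | 61% |
| 3% | 2.9 | 0.232 | 41% |
| 5% | 4.8 | 0.085 | 16% |
| 8% | 7.7 | 0.018 | 4% |
| 10% | 9.6 | 0.006 | 1% |

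If the rate in the hypertonic saline arm were half the control rate, the figures at control rates of 1, 2, 3, 5 and 10% would be 92, 76, 60, 36 and 9%.

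**Check within an adjusted model.** Trials were simulated with treatment, one binary covariate (35% prevalence) and one continuous covariate, and separation was tested by linear programming. The treatment coefficient was non-finite in about 85, 61, 40 and 16% of trials at 1, 2, 3 and 5%, in 3% at a rate of 8% and in 1% at 10%. This matches the closed form within simulation error. Counting trials in which any coefficient is non-finite, including separation on a covariate alone, gives larger figures: about 91, 76, 56 and 29% at 1, 2, 3 and 5%. Those describe failure of the model as a whole, not of the treatment estimate.

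**Instability where the estimate exists.** In the same simulated model, with no true effect, the treatment odds ratio was above 3 or below 1/3 in about 23, 18 and 14% of the finite fits at rates of 5, 8 and 10%. A second run gave 24, 18 and 16%. So when non-finite estimates become uncommon, at about 8 to 10%, extreme ones do not.

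All these percentages are conditional on the adjustment being triggered. The documents do not allow the probability of that to be computed.

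**The case against.** The strongest reply is that logistic regression is not the main analysis of these outcomes. Fisher's exact test is, and it remains valid with empty cells. Cell frequencies per group are already promised in the Statistics section. The regression enters only if baseline is uneven. Every affected outcome is exploratory, in a study that calls itself preliminary, and a divergent odds ratio is easy to spot. A fallback for sparse data could also sit in an analysis plan that is not shown, and the article does not rule out a penalised fit.

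Most of this stands, and it keeps the point small. Three stronger readings that a reader might infer are not supported:

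- **That the plan relies on logistic regression for death and dialysis.** It does not, because the Fisher comparison stands whatever the adjusted model does.
- **That the treatment estimate would usually be missing.** This depends on event rates that the documents do not give. Non-finite estimates are common up to about 3%, moderately frequent at 5% and uncommon from about 8%. The exclusions and the elective setting suggest few events but do not prove a rate.
- **That these are the trial's only harm data.** Electrolytes and acid-base status are also followed.

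What does not fall away is that the article states a method rather than leaving it open. Logistic regression is to be used for dichotomous outcomes once the condition is met, the condition has no threshold, and the only such outcomes named are the rare ones.

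**Conclusion.** The concern holds as a minor defect in a conditional, exploratory analysis. When the adjustment is triggered, ordinary maximum-likelihood logistic regression suits the named outcomes poorly at every rate examined. At assumed rates up to about 3% it gives no finite treatment odds ratio in about 41% of trials or more. At 5% that falls to 16%, with about five events to support the whole model. At 8 to 10% non-finite estimates are uncommon (4% and 1%), but eight to ten events remain too few for stable multivariable adjustment.

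The conclusion assumes equal event rates in the two arms and 48 analysed patients in each. The instability figures also assume two covariates of the kind simulated. The primary endpoint, the secondary endpoints and the sample size are not affected.

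**What to change.** In Statistical methods, restrict ordinary multivariable regression to interval outcomes. For renal replacement therapy and all mortality outcomes, keep the counts per arm and Fisher's exact test already planned, and add an exact confidence interval for the risk difference. If an adjusted figure is still wanted, state that it will come from Firth-penalised logistic regression with treatment and at most one covariate named before unblinding.

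The cost is a sentence or two in the protocol or analysis plan, with no effect on patient numbers or power. The downside is that there will be no conventionally adjusted odds ratio for these outcomes.

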#### Estimation of sample size

Sample size calculation was based upon fluid data from the Hemacetat study (NCT02895659) [28], conducted at our institution with the same patient collective. Preliminary data showed that patients received a mean of 3381 ml fluid during their ICU stay, with a standard deviation of 1734 ml. A clinically relevant effect size was determined to be a reduction of 1000 ml fluid (30%).

#### Rationale for effect size

Although several studies reported reduced infusion volumes when HS was used for fluid resuscitation [29], there is a large heterogeneity in studies on HS use, with widely varying amounts of sodium administered. In consequence, it was not possible to determine the amount of fluid to be saved when HS is used based on the available literature. Fluid overload is harmful in patients undergoing cardiac surgery and related to adverse outcomes [30–32] and thus should be avoided. However, the ideal amount of fluid for these patients is not yet clarified. In a pragmatic approach, we hence determined that it would be clinically beneficial if the total amount of fluid administered intravenously in the ICU (average 3381 ml at our institution) could be lowered by 1 L or 30%.

Modelling based on values of this study was achieved with the Power and Sample Size Calculator provided by the Statistical Institute of the Medical University of Vienna (http://statistics.msi.meduniwien.ac.at) and cross-checked on http://powerandsamplesize.com. The following constellations were obtained with regard to the required case numbers: n = 48 with a power of 80% and an α error of 0.05. Based on these results, a number of *n* = 48 patients with an IMP for each group, for a total number of 96 patients with an IMP, was determined to be sufficient.

### Ethical considerations

The study will be carried out in accordance with the protocol and with principles enunciated in the current version of the Declaration of Helsinki and the International Conference on Harmonisation (ICH) guidelines for Good Clinical Practice (GCP). The KEK and regulatory authorities will receive annual safety and interim reports and be informed if the study is discontinued, in agreement with local requirements. The KEK will be informed within 90 days if the study is discontinued.

All patients must give consent to participate in the study after receiving a detailed explanation of the potential benefits and harms. Patient information material as well as the consent form are included in the appendix of the study protocol. The KEK will receive a final report within 1 year of study termination.

### Premature study termination

The sponsor or investigator may terminate the study prematurely for a variety of reasons, including unforeseen ethical concerns, insufficient participant recruitment, doubts about the safety of the participants, or alterations in accepted clinical practice that make the continuation of a clinical trial unwise. For patients already enrolled in the study, treatment will be stopped immediately, while patient data will be recorded and observed until the patient leaves the ICU.

If the study has to be terminated prematurely, the regulatory authorities will be informed within 15 days.

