**Methods:**

In a prospective double-blind randomised controlled clinical trial, we aim to recruit 96 patients undergoing elective cardiac surgery for ischaemic and/or valvular heart disease. After postoperative admission to the intensive care unit (ICU), patients will be randomly assigned to receive 5 ml/kg ideal body weight HS (7.3% NaCl) or normal saline (NS, 0.9% NaCl) infused within 60 min. Blood and urine samples will be collected preoperatively and postoperatively up to day 6 to assess changes in renal, cardiac, inflammatory, acid-base, and electrolyte parameters. Additionally, we will perform renal ultrasonography studies to assess renal blood flow before, during, and after infusion, and we will measure total body water using preoperative and postoperative body composition analysis (bioimpedance). Patients will be followed up for 90 days.

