#### Fluid management and haemodynamic protocol in the ICU

On admission to the ICU, patients will receive 5 ml/kg ideal body weight of HS (7.3% NaCl) or NS (0.9% NaCl) by infusion pump for 60 min. Thereafter, ICU treatment will continue according to clinical routine.

If needed, norepinephrine is the first-choice vasopressor and will be titrated to a mean arterial pressure (MAP) judged adequate for the respective patient depending on age and history of hypertension and kidney injury. The range of target MAP is typically between 55 and 65 mmHg. Epinephrine will be added when an additional agent is needed to maintain adequate blood pressure, and if necessary norepinephrine will be exchanged for epinephrine. Dopamine is not used. In the presence of myocardial dysfunction — as suggested by increased cardiac filling pressures and low cardiac output — a dobutamine infusion will be administered. If patients become hypertensive, afterload will be reduced by nitroprusside natrium infusion.

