### End of study

For included patients, the study will start with admission to the ICU and will end after day 6. Thereafter, patients will be followed up for secondary endpoints. Patients will not be monitored further if they are readmitted to the ICU.

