### Statistics

Statistical evaluation will be conducted in the intent-to-treat population (carry forward last value method).

Descriptive presentation of the recorded data will be based on a scale type. Nominal/ordinal scales include cell frequencies at each level, missing data, valid number, and total number. Interval/proportional scales include arithmetic mean, standard deviation, median, spread, minimum, maximum, and valid number. In addition to the summary of the data using statistical parameters, descriptions will be provided individually for the total population as well as for both groups.

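### The early-termination rule provides for data only until ICU discharge and does not preserve the planned 30- and 90-day mortality follow-up of patients already infused

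*Protocol article*

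**What the plan says.** The section Premature study termination lets the sponsor or investigator stop the trial for several reasons, one of which is "doubts about the safety of the participants". A single rule then applies whatever the reason. "For patients already enrolled in the study, treatment will be stopped immediately", and "patient data will be recorded and observed until the patient leaves the ICU". No later data collection is mentioned for that case.

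The ordinary plan runs longer:

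- Abstract, Methods: "Patients will be followed up for 90 days". The same paragraph schedules blood and urine samples up to day 6.
- Outcome measures, Exploratory outcomes: "We will also analyse 30-day and 90-day mortality". Hospital stay and in-hospital mortality are listed there too, and the exploratory list under Objectives names the same mortality time points.
- End of study: the study itself closes after day 6. "Thereafter, patients will be followed up for secondary endpoints".
- Fluid management and haemodynamic protocol in the ICU: the study fluid is given on ICU admission "by infusion pump for 60 min".

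**The concern.** Stopping treatment and stopping observation are different decisions, and the termination rule sets an end point for both. Because the infusion takes one hour at ICU admission, nearly every patient inside the 90-day window on the stop date has already received it. Halting treatment changes nothing for them, while ending observation removes outcome data on people already exposed.

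This matters most when the trial stops for safety. Vital status of the most recently treated patients would then be part of the evidence on whether the doubt was justified. Under a literal reading it would be absent by rule, and the 30- and 90-day mortality comparisons would be incomplete for the last patients entered.

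**Working it through.** **Step 1. The windows side by side, reading the termination sentence literally**

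| Item | Planned window | After an early stop |
|---|---|---|
| Total fluid volume (primary) | ICU stay | kept |
| Early blood gas analyses | before infusion, 1 h after its end, then every 2 h for 6 h | kept while the patient is in the ICU |
| Blood and urine samples | up to day 6 | lost after ICU discharge |
| Hospital stay, in-hospital mortality | to hospital discharge | lost after ICU discharge |
| 30- and 90-day mortality | days 30 and 90 | lost unless that day was reached before the stop |

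**Step 2. How many patients could be affected**

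The plan gives no figure of its own here, so there is none to reproduce. The inputs are:

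- 96 patients receiving the study infusion (Population).
- First patient on 27 February 2018 and end of trial predicted for the end of 2019 (Trial status), which is 672 days.
- Assumption: even accrual.

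For a stop at least *w* days after the first patient, the expected number inside a window of *w* days is (96 / accrual days) × *w*.

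| Window | Accrual over 672 days | Accrual ends 90 days earlier (672 − 90 = 582 days) |
|---|---|---|
| 90 days | 96/672 × 90 = 12.9 | 96/582 × 90 = 14.8 |
| 30 days | 96/672 × 30 = 4.3 | 96/582 × 30 = 4.9 |
| 6 days | 96/672 × 6 = 0.86 | 96/582 × 6 = 0.99 |

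The second column covers the case in which the predicted end of trial includes the last patient's 90 days.

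For a stop before day 90 of recruitment the 90-day count is smaller. At day 45, for example, it is 96/672 × 45 = 6.4.

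As a share, 12.9/96 = 13% of the planned total. At a stop with 48 patients treated it is 12.9/48 = 27% of those treated.

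**Step 3. The narrower reading**

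If the sentence addresses only patients still in the ICU on the stop date, the count is the accrual rate times the ICU stay. The protocol does not give the ICU stay. For an assumed stay of 1 to 6 days it is 96/672 × 1 = 0.14 to 96/672 × 6 = 0.86 patients.

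**Step 4. What this means in deaths**

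The protocol gives no mortality rate. For an assumed 90-day mortality of 1% to 5%, 13 patients would yield 13 × 0.01 = 0.13 to 13 × 0.05 = 0.65 deaths. Some of these would occur in the ICU and be captured anyway.

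**The case against.** The strongest reply concerns the reading. The sentence pairs the end of treatment with observation in the ICU, so it may be aimed only at patients who are in the ICU when the trial stops, as an assurance that they remain observed. It fits poorly for someone discharged weeks earlier, and nothing in it expressly revokes the 90-day follow-up. That stands in part. It is why the count of 13 is an upper illustration, and why the finding is that the rule fails to preserve follow-up, not that the protocol forbids it.

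A second reply is that the article condenses protocol V1.3, which is not shown and may give termination procedures in full. That would answer a complaint about silence. Here, however, the article states an end point for data recording, and followed as written it departs from the plan elsewhere in the same article.

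Several stronger readings are tempting but not supported:

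- *The protocol contradicts itself in normal conduct.* It does not. The departure arises only on early termination.
- *A safety stop would lose the harm data.* The harms named under Safety measures during study conduct include electrolyte disturbance and acidosis, which are checked by blood gas analysis around and soon after the infusion, and those data are kept.
- *Day-6 values would be lost on a material scale.* Fewer than one patient is expected inside that window.
- *Renal replacement after ICU discharge would be lost.* The protocol gives that outcome no time window, and End of study says that patients readmitted to the ICU are not monitored further.
- *Missing patients would be counted as alive at day 90.* A reader might infer this from the last-value-carried-forward rule under Statistics, but that section does not say the rule applies to mortality.

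**Conclusion.** The point holds as a badly fixed rule of small consequence. On premature termination, including for safety doubts, the protocol provides for data only to ICU discharge and does not preserve the 90-day follow-up or the 30- and 90-day mortality it plans elsewhere.

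On the literal reading, up to about 13 patients lose day-90 vital status and about 4 lose day-30 status, or about 15 and 5 with the shorter accrual period. These counts rest on even accrual and a stop after the first 90 days of recruitment. On the narrower reading, the number is below one for ICU stays of up to 6 days. Patients past day 90 at the stop lose nothing.

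The outcomes affected are exploratory mortality, in-hospital outcomes and a negligible number of day-6 assessments. The primary endpoint is confined to the ICU stay and is intact. The change is worth making because it costs little, not because the trial's main result is at risk.

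**What to change.** Reconcile Premature study termination with the Abstract, Exploratory outcomes and End of study by adding one sentence: on premature termination, patients already randomised complete the planned data collection (scheduled assessments to day 6, and 30- and 90-day vital status) unless they withdraw consent.

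This concerns data collection only and leaves the protocol's provisions on treatment untouched. The cost is one sentence in an amendment, plus follow-up contacts that normal conduct already plans for these patients, about 13 to 15 at most under the assumptions above.
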